### Sample size

First, we have carried out the theoretical calculation of the sample size for the definitive study (*n* = 265), based on the following premises: 1) Three study arms: *maximum intervention group*, pedometer + goal + recall (I1): minimum absolute reduction in the prevalence of low compliance with recommendations that are statistically significant to be detected, that it is 15% with respect to I1*; minimum intervention group*, pedometer (I2): minimum absolute reduction in the prevalence of low compliance with recommendations that are statistically significant to be detected, that is 30% with respect to C; and control group (C), with an estimated prevalence of low compliance with physical activity recommendations of 50% [12, 13]. 2) Alpha error: 5%; 3) Power of the study: 80%; 4) Comparison of I1 vs I2: from the previous premises, 120 women would be needed in each arm; Comparison of I1 vs C: from the previous premises, and taking as reference the 120 women of the I1 arm required for the previous comparison, 25 women in the C arm would be required.

A pilot of the previous design was carried out with 72 women not included in this study: 24 women in each arm of the study, interviewed twice (12th and 20th GW), during the months of February to May 2018. The recruitment period was 3 months. To select a total of 265 women, 1 year and 7 months would be required (considering holiday periods and Covid-19). We estimate 20–30% of losses in second and third interviews (due to neonatal loss or abandonment of the study).

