### Randomization of participants and concealment

The Stata Ralloc program will generate a randomization sequence by blocks of *n* = 9 and 3 arms per block (A, B and C). In this way, each block of nine pregnant women treated consecutively will be assigned, in a random order, to the arms C (control), I1 (Intervention 1) and I2 (Intervention 2): *C I1 I1 I1 I1 I2 I2 I2 I2*, up to complete the assignment of the 265 pregnant women. The sequence will be generated by the data analysts and kept in the monitoring centre, remaining at all times hidden to those clinicians responsible for the enrolment of pregnant women. Allocation sequence will be concealed until women are assigned to interventions by the research staff/interviewer. This way, the follow-up centre will be contacted each time the interviewer has a pregnant woman, so that they are informed of the arm to which she will be assigned.

There will be concealment for the people in charge of carrying out the evaluation and analysis of the data because they will manage the database without personal women information or knowledge about the group intervention, where women will be allocated. Due to the nature of the study, neither the participants nor the professionals who indicate the intervention can be blinded. Participants will know they will be selected for either a pedometer group or a non-pedometer group. They will not know if the intervention is minimum (pedometer only) or maximum (pedometer and a goal of 11,000 steps/day).

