### Data analysis

A descriptive analysis of the variables collected in the study will be carried out. Measures of central tendency and dispersion will be calculated for the numerical variables and absolute and relative frequencies for the qualitative ones. The normality of the variables will be checked with the Kolmogorov-Smirnov test, in order to determine whether parametric or non-parametric tests will be carried out later. 95% confidence intervals (CI) will be obtained for both means and proportions.

For the contrast of the hypothesis of equality between the group of patients I1 and the group of patients I2, in terms of the number of daily steps and for each GW (19th and 31st), the Student t test will be used for independent samples or Mann-Whitney U, as appropriate. Subsequently, to assess whether there are differences between the groups with respect to the frequency of insomnia/quality of life for each trimester of pregnancy, the Pearson’s Chi-square test or Fisher’s exact test will be used when necessary.

On the other hand, to determine if differences are found between the quantitative variables (hours of sleep, quality of sleep) throughout the study period (first, second and third trimester) among the participants, the analysis of variance will be used for measurements repeated in the parametric case. In the case of having to use a non-parametric test, the Friedman test will be used. Subsequently, to assess the differences in the quality of life, for each of the groups, before starting the walking program and after finishing it (pre-post), the McNemar-Bowker test will be used.

For the contrast of the hypothesis of equality between the three groups of patients, regarding the weight gained during pregnancy (until 34 ^st^ GW), the weight of the newborn and the gestational week, an analysis of the variance or the test of Kruskall-Wallis will be used, as appropriate. In case of statistical significance, multiple comparisons will be obtained using the Student’s parametric test or the non-parametric Mann-Whitney U test applying Bonferroni correction.

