Finally, a bivariate mixed-effects logistic regression model will be carried out to determine which variables influence the greater frequency of insomnia, considering the latter quantitatively. To delimit the extent to which the associations that appear are explainable by the effect of the rest of the variables included in the study, a multivariate mixed-effects logistic regression model will be constructed. 95% confidence intervals (CI) will be obtained. All contrasts will be bilateral and statistical significance will be considered when the *p* value is ≤0.05. The data analysis will be carried out by intention to process and by protocol, using the Stata / SE v15.0 statistical package.

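### Weight gain, newborn weight and gestational week: ANOVA and Student tests across 4:4:1 arms hold their level only if spread is equal; naming the Welch versions is a cheap improvement

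*Protocol article*

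**What the plan says.** The Data analysis section of the protocol article compares the three arms on weight gained in pregnancy, newborn weight and gestational week. The overall test is stated as "an analysis of the variance or the test of Kruskall-Wallis will be used, as appropriate". If it is significant, "multiple comparisons will be obtained using the Student’s parametric test or the non-parametric Mann-Whitney U test applying Bonferroni correction".

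The rule for choosing between the two families of test is given earlier in the same section: "The normality of the variables will be checked with the Kolmogorov-Smirnov test, in order to determine whether parametric or non-parametric tests" will follow. No check of spread is mentioned, and no unequal-variance version is named. All tests are two-sided at 5%.

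The section on randomization and concealment fixes blocks of nine as "C I1 I1 I1 I1 I2 I2 I2 I2", that is, one control for every four women in each pedometer arm. The Outcome measures section lists these three variables among the other pre-specified outcomes, below the primary and secondary ones.

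**The concern.** Classical ANOVA and the Student t test estimate one common variance. When arms are of similar size, moderate differences in spread do little harm. Here the control arm is a quarter of the size of each pedometer arm. The pooled variance therefore comes almost entirely from the pedometer arms, while the real uncertainty of any contrast with control comes mainly from about 29 women. If controls are more variable than the others, the tests reject too often; if they are less variable, too rarely. A normality check cannot detect either case.

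At stake is the calibration of p values, and of any pooled-variance intervals, for the comparisons with control on maternal weight gain, newborn weight and gestational age.

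**Working it through.** **Inputs from the protocol.** Total 265 women and a 1:4:4 block. 265 × 1/9 = 29.4 and 265 × 4/9 = 117.8, hence about 29 controls and 118 in each pedometer arm. (The Sample size section works with 25, 120 and 120.) Level 5%, two-sided. Three pairs, so the Bonferroni level is 0.05/3 = 1.67% for each pair.

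**Assumed input.** The ratio r = control SD / pedometer-arm SD. The documents give no SDs, so r is varied.

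**Simulation.** Normal outcomes with equal means, arms 118/118/29, 100,000 runs for each ratio. The gated column requires both a significant ANOVA and a pairwise Student p value of at most 1.67%.

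| r | ANOVA (nominal 5%) | Gated, Bonferroni-corrected Student, I1 vs C (nominal 1.67%) | Welch ANOVA (nominal 5%) |
|---|---|---|---|
| 0.67 | 2.7% | 0.2% | 5.0% |
| 0.8 | 3.3% | 0.6% | 4.9% |
| 1 | 5.0% | 1.5% | 5.0% |
| 1.25 | 7.8% | 3.4% | 4.9% |
| 1.5 | 11.4% | 5.9% | 5.0% |

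The row r = 1 reproduces the plan's own 5%. Repeat simulations agree within about 0.2 points. With arms of 120/120/25, ANOVA gives 2.7% at 0.67 and 12.0% at 1.5. Losing about 25% to 30% of women hardly changes the ANOVA results (2.7% to 2.8%, and 11.4% to 12.0%).

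**Hand check of the pairwise test.** With the pedometer-arm variance set to 1:

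- True variance of the difference: 1/118 + r²/29.
- Variance the Student test uses, on average: [(117 + 28r²)/145] × (1/118 + 1/29).
- The nominal critical value at 1.67% is z = 2.394. The effective one is 2.394 divided by the square root of true over used variance.

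For r = 1.5: true = 0.00847 + 0.07759 = 0.0861; used = 1.241 × 0.0430 = 0.0533; square root of the ratio = 1.27. The effective z is 2.394/1.27 = 1.88, a rejection rate of about 6%.

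For r = 0.67: true = 0.00847 + 0.01533 = 0.0238; used = 0.893 × 0.0430 = 0.0383; square root of the ratio = 0.79. The effective z is 2.394/0.79 = 3.04, about 0.24%.

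Both agree with the simulated corrected test before the ANOVA gate (5.9% and 0.24%).

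**The non-parametric route.** Kruskal-Wallis with the same arms (6,000 runs) rejects 3.6% at r = 0.67 and 8.3% at r = 1.5. It drifts less than ANOVA but does not remove the problem.

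**The case against.** The case against is substantial.

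- **Nothing suggests unequal spread.** If walking affects nobody, randomised arms have the same spread and the level is 5%. A ratio of 1.5 means a 2.25-fold variance ratio, which is large. The Background section cites reduced weight gain in obese pregnant women, so response could be uneven, but plausible versions of that give smaller ratios. Suppose 20% of women start 1 SD above the rest and the intervention removes the whole gap: the ratio is √(1 + 0.2 × 0.8 × 1²) = 1.08. With 30% and 1.5 SD it is √(1 + 0.3 × 0.7 × 1.5²) = 1.21. Such an effect also shifts the mean, so a rejection would not be a false positive. *This stands* as a reason to give more weight to the 0.8 to 1.25 range. It is not complete. The level of a pooled interval does not depend on the mean difference: at r = 1.5 the uncorrected Student test for I1 vs C rejects 12.4%, so a pooled 95% interval would cover 87.6% even with a real effect. The protocol also expects 20% to 30% losses in an unblinded trial, and these could alter the observed spread.

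- **The article leaves detail to an analysis plan.** The wording leaves room for judgement, and equal variance is inferred from the test names. *This stands in part.* But the article does state a selection rule, and that rule looks only at normality.

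- **A reader might infer an error rate of 1% to 12% instead of 5% for every comparison with control.** The documents do not support that. Both ends come from a single Student test at an uncorrected 5%, with no prior overall test, which the protocol does not plan. The planned pairwise tests are gated and corrected, so their reference is 1.67%. The overall ANOVA does not fall to 1%. In a simulation of the planned sequence, the chance of any false claim against control was 5.3% at r = 1.25 and 8.1% at r = 1.5, so it is not more than twice 5% either. I1 versus I2 has equal arms and is essentially unaffected.

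**Conclusion.** The point holds as a low-severity improvement. The tests as named rely on equal spread in a 4:4:1 design, and the only stated check does not address spread. Over an assumed control-to-pedometer SD ratio of 0.8 to 1.25, the ANOVA level is about 3% to 8% instead of 5%, and the planned I1 versus control test runs at about 0.5% to 3.5% instead of 1.67%. Over 0.67 to 1.5 the ranges are about 3% to 11.5% and 0.2% to 5.9%. Bonferroni correction lowers the absolute rates but does not restore the nominal level: at 1.5 the pairwise test rejects about 3.5 times as often as intended (5.9/1.67).

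These figures assume normal outcomes, equal means and SD ratios that the documents do not give. They do not show that the trial's p values will be wrong. If spread is equal, nothing is lost by the current wording. The primary and secondary outcomes are not touched by this point.

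**What to change.** In the Data analysis section, for weight gain, newborn weight and gestational week, name Welch's ANOVA as the parametric overall test and Bonferroni-corrected Welch t tests as the parametric pairwise tests. Report Welch 95% confidence intervals for I1−C, I2−C and I1−I2. In the simulations Welch's ANOVA stayed at 4.9% to 5.2% for SD ratios from 0.5 to 2 and at all arm sizes tried.

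The cost is one sentence of wording and, if variances turn out equal, about 1 to 2 points of power. For example, for a difference of 0.6 SD between I1 and control at an uncorrected 5%, power is 80.9% with Welch against 82.3% with Student. The change does not cure the smaller drift of the Kruskal-Wallis route, so the Welch intervals are worth reporting whichever test is chosen.

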**Methods:**

Randomized Controlled trial in parallel in healthy sedentary pregnant women (*n* = 265), Walking_Preg Project (WPP), from university hospital in Granada, Spain. At 12th gestational week (GW), they will be invited to participate and randomly assigned to one of the three arms of study: the intervention group I1 (pedometer, goal of 11,000 steps/day), intervention group I2 (pedometer, no goal) and control (no pedometer). Duration of intervention: 13–32 GW. At 12th, 19th and 31st GW the average steps/day will be measured in groups I1 and I2. At 13th, 20th and 32nd GW, Athens Insomnia Scale (AIS), Pittsburgh Sleep Quality Index (PSQI), Adherence to Mediterranean Diet (AMD), physical activity (short IPAQ), quality of life (PSI), and consumption of toxic substances (caffeine, illegal drugs, alcohol and tobacco) will be collected. Student t test or Mann-Whitney U will be used to compare 19th and 31st GW mean of daily steps between I1 and I2 groups. To compare differences between groups in terms of frequency of insomnia/quality of life for each trimester of pregnancy, Pearson’s Chi-square test or Fisher’s exact test will be used. To determine differences in hours of sleep and quality of sleep throughout each trimester of pregnancy, analysis of variance or Friedman test will be used. McNemar-Bowker test will be used to assess differences in life quality in pre-post analyses in the 3 arms. We will use Stata 15 statistical software.

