## Background

The prevalence of insomnia at the beginning of pregnancy is around 40%, reaching over 60% in the third trimester of pregnancy [1–4]. Insomnia is associated with an increase of gestational diabetes mellitus (GDM), depression in pregnancy and postpartum, arterial hypertension and preeclampsia as a result of the increase in cytokine levels derived from sleep deprivation [5]. Insomnia is also involved in unplanned caesarean sections, prolonged labour, premature placental abruption, delayed intrauterine growth and prematurity [6].

It has been documented that practice of physical activity (PA) prevents the onset of insomnia in adults [7], postmenopausal women [8] and pregnant women [9]. In addition, the practice of regular PA (> 150 min/week) also increases the quality of sleep in adults [10] and in pregnancy [11]. However, only 20.3–30% of pregnant women are active [12, 13]. In fact, pregnant women spend more than 50% of their time in sedentary activities [14]. To make an objective assessment of this, a woman who counts less than 5000 steps/day on average could be considered sedentary [15].

Walking is one of the recommended activities in the guidelines of PA in pregnant women in Canada, Japan, Norway and Spain and the most carried out during pregnancy [16, 17]. However, the number of steps/days counted in the first trimester of pregnancy does not exceed 5000 steps [18], which is half of those recommended (10,000-11,000) [19] and decreases as the gestation progresses [18]. Walking during pregnancy regulates, prevents or delays the increase in blood pressure and cholesterol in healthy women [20], decreases the prevalence of type 2 diabetes mellitus [21] and improves glycaemic control of pregnant women with GDM [22]. Moreover, improves cardiorespiratory capacity [23], decreases stress and anxiety and improves sleep quality [24], increases quality of life [25] and reduces weight gain during pregnancy [26].

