### Selection criteria for eligibility

Inclusion Criteria: 1) Pregnant women with a minimum of 18 and maximum of 49 years of age; 2) Low medical risk pregnancies that will be attending in the Unit of Obstetrics and Gynecology, in a public third level Maternity Hospital in Granada (Spain); 3) Sedentary women (< 5 days/week of moderate-vigorous physical activity at least > 30 min.; equivalent to < 7000 steps/day); 4) With mobile phone and e-mail; 5) Without intellectual deficits or difficulty to understand the language.

Exclusion Criteria: 1) Chronic disease: diabetes, high-pressure, cardiac or respiratory disease, liver or kidney disease or mobility problems; 2) Women with relative or absolute repose needed; 3) Active women (> 5 days/week of moderate-vigorous physical activity at least > 30 min.; equivalent to > 7000 steps/day); 3) Insomnia at beginning of pregnancy or having drugs for sleep problems.

The study sample will consist of women who, meeting the inclusion criteria, agree to participate, upon request for voluntary collaboration and signing of two documents: 1) Informed consent approved by the Provincial Ethics Committee of Granada and 2) Pedometer loan certificate.

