### Location and data collection

The collection of the study sample began in June 2019 in the Obstetrics and Gynecology Department, where the first uterine ultrasound is performed at 12th GW. The Service Management Unit of Obstetrics and Gynecology of the Maternal and Child Hospital –Virgen de las Nieves University Hospital Complex, in Granada– is the centre of care reference in the northern area of Granada, a third level hospital that serves a reference population of 439,035 corresponding to a sector of the Granada Metropolitan District and the Basic Health Zone of Alcalá la Real, Jaén. It has been a reference of the Northeast Health Management Area of Granada.

Walking_Preg Project (WPP) schedule of enrolment, interventions, and assessments is shown in Fig. 1. The health staff will inform each woman of the study by referring them to an adjoining consultation enabled for a member of the research team at the hospital. All women who meet the inclusion criteria and sign the informed consent and loan certificate will be invited to participate in the study to reach target sample size. During the pregnancy, three interviews will be conducted by training staff (12th, 20th and 32nd GW), collecting the information in an access database. The period of recruitment of pregnant women will end in December 2020. We have stopped the recruitment from March to August 2020, because of Covid-19. The period of follow-up of women in the study will take place from the time of recruitment of women (12th GW) until delivery.

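### The one-predictor mixed models for insomnia contain no gestational-visit term, so covariates that drift over pregnancy can show spurious associations; the article does not say that the multivariable model corrects this

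*Protocol article*

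**What the plan says.** The last paragraph of Data analysis plans two steps. In the first, "a bivariate mixed-effects logistic regression model will be carried out to determine which variables influence the greater frequency of insomnia". In the second, to see how far those associations are "explainable by the effect of the rest of the variables included in the study", "a multivariate mixed-effects logistic regression model will be constructed". No covariate list is given for the second step, and gestational week at interview is neither named nor excluded.

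Other sections give the setting:

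- **Repeated measurement.** "three interviews will be conducted by training staff (12th, 20th and 32nd GW" (Location and data collection). The insomnia scale is part of each interview (Instruments). There is one hospital.
- **Trend in insomnia.** "The prevalence of insomnia at the beginning of pregnancy is around 40%, reaching over 60% in the third trimester of pregnancy" (Background).
- **Trend in walking.** The Background says that the daily step count "decreases as the gestation progresses", without giving the size of the fall.
- **Entry restriction.** The exclusion criteria include "Insomnia at beginning of pregnancy or having drugs for sleep problems".
- **Step records.** "the average steps/day will be measured in groups I1 and I2" (Abstract, Methods), so controls have none. The short IPAQ, caffeine, medication and pregnancy symptoms are collected in all three arms at the interviews.

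**The concern.** A mixed-effects model makes sense here only if it uses the repeated interviews, and with one centre the natural cluster is the woman. If so, each one-predictor model compares insomnia across visits as well as across women, with nothing to represent how far the pregnancy has advanced. Insomnia becomes more common with gestation in everyone. A covariate that also changes with gestation will then track insomnia even if the two are unrelated at any given week.

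This is the analysis from which the article intends to say which variables influence insomnia. Read as planned, the first step could report that less activity, more medication or more symptoms go with insomnia when all of them merely change with the stage of pregnancy. The sign is not predictable. If steps fall naturally, walking looks protective; if the intervention raises steps while insomnia rises, walking looks harmful.

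**Working it through.** **1. Why the random intercept does not help.** Let the truth be logit P(insomnia for woman i at visit t) = a_t + u_i, with a covariate X_it = m_t + v_i + e_it that has no effect. The planned first step fits logit P = b0 + b1·X_it + u_i. Within one woman u_i is constant, but a_t still changes from visit to visit. The only term that can absorb that change is b1·X_it, so b1 takes the sign of the covariance between a_t and m_t across visits. If m_t is flat, b1 is about zero. If a visit effect is added, it takes up a_t and b1 returns to about zero.

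**2. Size.** The article states no figure to reproduce, so the size was simulated. From the article come the three visits, the 40% to 60% rise, the total of 265 women and the two-sided 5% level. The drift and variance components are assumptions. All fits are maximum-likelihood random-intercept logistic models with a likelihood-ratio test.

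*Set A.* 265 women, 25% missing at the last visit (the article expects 20–30% losses), random-intercept SD 1.5, within-woman correlation of the covariate 0.5; 1,000 trials per scenario (300 for the 0.1 SD drift).

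| Insomnia by visit | Covariate drift per visit | False positives, no visit term | With visit term |
|---|---|---|---|
| 40/50/60% | 0.1 SD | 7.7% | 7.7% |
| 40/50/60% | 0.25 SD | 20.5% (OR 0.89 per SD) | 5.8% |
| 40/50/60% | 0.5 SD | 58% (OR 0.81 per SD) | 5.8% |
| 40/60%, two visits | 0.25 SD | 12% | 5.2% |
| 40/60%, two visits | 0.5 SD | 27% | 5.2% |

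*Set B.* 240 women, random-intercept SD 1.0, steps with SD 1,500 between and 1,500 within women; 100 trials per scenario.

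| Insomnia by visit | Mean steps by visit | OR per 1,000 steps and false positives, no visit term | With visit term |
|---|---|---|---|
| 40/50/60% | 5,500 throughout | 1.00, 3% | 1.00, 4% |
| 40/50/60% | 6,000/5,500/5,000 | 0.95, 27% | 0.99, 3% |
| 5/35/60% | 6,000/5,500/5,000 | 0.91, 77% | 0.99, 5% |
| 40/50/60% | 5,000/6,500/7,000 | 1.07, 45% | 1.00, 9% |

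With 100 trials, the standard error of a 5% rate is √(0.05 × 0.95/100) = 2.2 percentage points, so 3% to 9% is compatible with 5%.

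**3. The two sets agree.** In set B the total SD of steps is √(1,500² + 1,500²) = 2,121, so a fall of 500 per visit is 500/2,121 = 0.24 SD. The OR of 0.949 per 1,000 steps becomes 0.949^2.121 = 0.895 per SD, against 0.89 in set A at 0.25 SD. The flat-steps row isolates drift as the cause.

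**4. If arm is the single predictor.** The Discussion aims at 33% less insomnia than about 60%, that is 60% × (1 − 0.333) = 40%. Assume that full effect at 32 weeks, half of it at 20 weeks, none at the first interview, random-intercept SD 1.5 and arms of 120/120/25. The pooled odds ratio for I1 against control is then about 0.6 (0.62 with no insomnia at the first visit, 0.59 with 40%; 200 trials). The conditional odds ratio at 32 weeks is 0.32. The pooled value averages over a visit before the intervention and does not describe the third trimester.

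**The case against.** The strongest reply is that the one-predictor step is only a crude screen and that adjustment is the declared second step. The article gives no covariate list for that step, and such a list is commonly left to the full protocol or analysis plan. This stands in part. A reader might infer that all the planned models are one-variable-at-a-time, or that the multivariable model leaves visit out. The document supports neither: a multivariable model is planned, and on visit it is silent. Elsewhere in Data analysis the authors do treat trimester as a factor. The one-predictor step is different, because what it contains is stated.

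A reader might also infer that walking is the main casualty. The article does not name steps as a predictor, has them only in the two pedometer arms, and cites a natural decline that an intervention with a goal may reverse. Walking is one example among several, and the direction of bias is not fixed.

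The size is open to challenge too. No document gives the drift, the random-intercept SD or the within-woman correlation, and a small drift does no visible harm. Assuming no insomnia at all at the first interview (0/30/60%) gave rates of 81% and about 100% in set A. These are not relied on: the article does not tie the entry exclusion to a cutoff on the insomnia scale, and no model with visit was fitted for comparison.

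The form of the model is itself partly a reading. The article does not spell out the random effect, and it pairs logistic regression with insomnia taken as a quantity. A linear mixed model of the score without visit would be confounded in the same way.

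On arm, the pooled and the 32-week odds ratios are different quantities, and the article does not present this model as its estimate of the randomised effect. That is accepted; the arm result is a caution about interpretation.

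**Conclusion.** The point holds for the first modelling step and, as an open question, for the second. Carried out as written over the repeated interviews, the one-predictor models confound any gestation-dependent covariate with gestation itself. With a moderate drift (about 0.25 to 0.5 SD per visit, or the step changes in set B), false-positive rates were about 12% to 77% against a nominal 5%, and close to 5% with visit included. At 0.1 SD per visit there was no clear inflation. These figures rest on assumed drift and variance components and on the woman being the random effect.

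It would be wrong to conclude that the trial's primary insomnia comparison is compromised. That comparison is made between randomised arms within each trimester by chi-square or Fisher's exact test, where visit is fixed by design. The point concerns a secondary, exploratory analysis. It is still more than a missing detail, because following the stated step gives time-confounded associations and a better method is available from data already collected.

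**What to change.** In the last paragraph of Data analysis:

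- State that interview visit (gestational week) enters as a categorical fixed effect in both the one-variable and the multivariable mixed models, and describe the one-variable results as adjusted for visit.
- When arm is a predictor, include arm-by-visit and report the contrast at 32 weeks.
- If the exclusion of insomnia at the beginning of pregnancy leaves essentially none at the first interview, model the outcome at the 20- and 32-week visits only.

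The cost is one sentence, no new data, and two degrees of freedom per model with three visits or one with two. In an arm model the interaction adds (3 − 1) × (3 − 1) = 4, or 2 with two visits. Some apparent associations may disappear, which is the purpose of the change.
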